## 1. Introduction

During intensive development phases, such as pregnancy and childhood, the probability of insufficient nutrient supply rises [1]. In the course of a vegan diet, the focus should be on an adequate supply of vitamin B12, zinc, iron, calcium, vitamin D, iodide, and omega-3 fatty acids [2,3,4,5]. Nutrient deficiency can be prevented by supplying these critical nutrients of a vegan diet adequately, with specific foods or with DS [6,7,8]. A vegan diet is defined as a dietary pattern that excludes all animal-derived products—including meat, fish, dairy, eggs, and honey—and is based on the consumption of plant-derived foods such as fruits, vegetables, grains, legumes, nuts, and seeds [9]. A purely plant-based diet can provide all necessary macro- and micronutrients during pregnancy and childhood, except for a possible lack of docosahexaenoic acid (DHA) and eicosapentaenoic acid (EPA), as well as vitamin B12 [10]. Newborns of vegan mothers are on average smaller (small for gestational age) and are often born with a lower birth weight than those born from omnivores [11,12], which could lead to further nutrient-deficiency-related development and health impairments. If mothers lack an adequate supply of nutrients in their diet, nutrient deficiencies can occur in infants despite breastfeeding [13,14,15,16,17,18,19]. Expert groups such as the Academy of Nutrition and Dietetics (AND), the German Nutrition Society (DGE), and the Austrian Nutrition Society (OEGE) partly disagree about the risks of a purely plant-based diet for pregnant women, infants and children [20]. The AND considers a well-planned vegan diet to be safe, even during vulnerable stages such as pregnancy and childhood [21]. Although the DGE neither clearly supports nor rejects a vegan diet during the mentioned life phases, it points out insufficient data and the need for comprehensive nutritional skills for safe implementation [22]. The OEGE does not recommend a vegan diet during pregnancy and childhood due to the risks of possible malnutrition and possible associated impairments [23]. All organizations share the common point of view that a vegan diet during life phases such as pregnancy, infancy and childhood should be preceded by comprehensive planning with special emphasis on critical nutrients of a vegan diet—especially vitamin B12 supplementation. In the past no distinct statements were made on the benefits or drawbacks for vegan pregnant women and their children in terms of nutrient supply, due to a lack of studies with a sufficiently large number of participants or inadequate significance [24,25,26]. The latest findings show that there are risks of malnutrition, which can be prevented by the use of DS and observing the health and developmental status of mother and child [27,28]. Although the selection of vegan foods is becoming more diverse, there is no data on whether this expansion of what is on offer results in a better nutrient supply for vegans—the current state of studies suggests dietary supplementation is necessary [29,30,31]. Pregnant women who consume an omnivorous diet usually take DS to support the healthy development of their unborn children [32]. Influential factors that affect the approach of vegan pregnant women and parents towards DS have not yet been scientifically determined. It has been shown that mothers of vegan-fed children have less nutritional knowledge than mothers whose children follow an ovo-lacto-vegetarian diet [33]. Parents frequently ask pediatricians how to provide the most balanced diet for their children [34,35]. For this reason, constructive communication between parents of vegan-fed children and their pediatricians and dieticians is important to make comprehensive information about a healthy, purely plant-based diet available [36,37]. Despite frequent uncertainty about the safety of DS due to varying production standards regarding different origins and manufacturers, the market for supplements and botanicals is expanding [31]. Compared to pharmaceuticals, DS are subject to food law and are, therefore, liable to less strict controls [38]. An official approval process, that is required for pharmaceuticals and takes many years, is not obligatory for DS. This can have an impact on the safety and harmlessness of their consumption. Preparations that consumers buy online are often of inferior quality. Ingredients are inadequately declared and can even be detrimental to the health of consumers because of different regulations in different parts of the world, which is why customers and patients should be comprehensively informed by medical experts [39]. Additionally, adulterations can cause harmful health impacts [40]. Non-prescription DS compared to prescription DS are often characterized by insufficient information on ingredients, dosage and intake [41]. This represents a major risk, especially for pregnant women and children [42]. The relationship between vegan parents and especially physicians can, therefore, influence the health and well-being of vegan-fed children. However, the majority of pediatricians is perceived skeptical or negative towards a vegan diet, which can affect vegan parents’ trust in their children’s physicians and limit or prevent communication [34,43]. Many parents do not inform pediatricians about their children’s vegan diet in order to avoid being exposed to criticism [34]. A skeptical attitude of physicians could result from legitimate, nutrition-related objections on the one hand and from a lack of knowledge about a vegan diet and DS on the other [44]. This can lead to health impairments for vegan pregnant women and children due to a lack of information supply and miscommunication. It is not yet clear whether other specialists and medical experts, in addition to pediatricians, have a negative attitude towards a vegan diet during pregnancy and childhood and, therefore, offer little or no advice on vegan diets and DS. If a negative attitude also exists among gynecologists, general practitioners, dieticians and pharmacists, this could have a negative health- and nutrition related effect on vegans due to a lack of information transfer. The level of information and the associated information provided by medical experts on a vegan diet and DS during pregnancy and childhood, therefore, has a significant impact on the adequate nutrient supply of vegans. The level of knowledge among medical experts regarding a vegan diet and DS has not yet been sufficiently examined. Competent advice on supplementation with DS is essential for a healthy development during pregnancy and childhood. If information is not provided by medical experts, vegans use other sources of information, particularly social media. It can be assumed that many vegans are insufficiently, incorrectly or not at all informed about DS and a well-balanced vegan diet due to the different quality of disposable information. Dubious sources of information and influential factors (e.g., social environment, internet and social media, magazines, advertisement) are likely to make parents feel insecure and can affect the health of their children. A lack of expertise on the part of vegan pregnant women and parents (on a vegan diet and DS) and insufficient support from medical experts (pediatricians, gynecologists, general practitioners, pharmacists, dieticians) entail possible health risks. The impact of medical expertise and other social, sociodemographic factors (e.g., age, social environment and background, internet and social media, advertising), on the diet of vegan pregnant women and children (up to the age of 5 years), as well as on supplementation with DS needs to be investigated. Whether and to what extent external factors influence a vegan pregnancy, infancy and childhood have not yet been comprehensively investigated. In addition, there is still no data on the opinion and level of knowledge of consulting medical experts and associated consequences regarding nutrition and the possibility of supplementing DS for vegans.

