##### Opinions and General Knowledge of Medical Experts About a Vegan Diet and Dietary Supplements (For a Vegan Pregnancy, Infancy and Early Childhood) Should Be Established

The impact of expert opinion and knowledge on a vegan diet regarding their advice on DS for vegans (during vegan pregnancy, infancy and early childhood) should be clarified. Statistically evaluated results of the survey should allow conclusions about the influence of information supply by medical experts on nutrient supply, of vegan pregnant women and growing children (up to the age of 5 years). A possible misinterpretation of the health risk of a vegan diet during pregnancy, infancy and early childhood due to insufficient knowledge of DS could increase health risks.

A negative basic attitude towards a vegan diet influences the relationship of trust between vegans and their physicians. If there is no advice on DS, health risks can increase.

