#### 2.1.2. Secondary Objectives

##### Determination of the Level of Knowledge of Vegans on Dietary Supplements, Nutrient Deficiency Risks and Correct Dosage of Dietary Supplements During Pregnancy, Infancy and Early Childhood (Up to the Age of 5 Years)

If the risk of incorrect dosage of DS is misjudged by vegans during pregnancy, infancy and early childhood, nutrient deficiencies or overdose with DS become likely. Risks of nutrient deficiency due to missing intake or incorrect selection of DS because of a lack of food and nutritional health literacy should also be cognizable. Avoiding these circumstances would require a competent information provision for vegans by medical experts (pediatricians, gynecologists, general practitioners, pharmacists, dieticians). Imprecise advice could affect the relationship of trust between medical experts and vegans as well as the nutrient supply during pregnancy, infancy and early childhood.

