##### Determination of Compliance with Dietary Supplements During Pregnancy, Infancy and Early Childhood as Well as the Consequences of Administration Difficulties to Vegan-Fed Children (Up to the Age of 5 Years)

It will be investigated whether vegans consider regular intake or administration of DS during pregnancy, infancy and early childhood to be effective. In addition, it should be clarified whether certain dosage forms (e.g., drops, pills, capsules) of existing DS for infants and children represent an unsettling factor for vegan parents, which in turn increases the risk of incorrect dosage and resulting nutrient deficiencies (e.g., wrong administration, wrong dosage). Medical experts should also evaluate the options of dosage forms and compliance as well as the consistency of administration by parents to their vegan-fed child. This should clarify whether dosage forms of DS can have an impact on the regularity of administration and subsequently on the development of nutrient deficiencies. Statements about the regularity, duration of intake and compliance of DS are intended to allow conclusions about the supply of consumers with the corresponding DS and to show any potential dangers or health-enhancing effects.

If vegans indicate a high level of compliance when taking DS, the willingness to take DS is obvious and the relevance of competent expert advice on DS can be strengthened.

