
Research gaps concerning the administration of DS, the consistency of taking them and compliance shall be closed by statistically evaluating data from performed surveys (vegans, pediatricians, gynecologists, general practitioners, pharmacists, and dieticians). In addition, causes for the intake or rejection of DS (from a social and socio-demographic perspective) are to be examined. Resulting risks concerning the supply of nutrients are to be determined as well as the role that information sources play in this context. It is precisely these unanswered questions that underline the relevance of the VedieS study, as they are directly related to risk prevention. According to a recent study by Meulenbroeks et al. [61], pregnant women following a vegan diet often receive limited or no specific dietary guidance from obstetric healthcare providers. Only 19% of participants reported having received nutritional counseling that was specific to their needs during pregnancy. The VedieS study’s approach to identifying the cause of nutrient deficiencies during vegan pregnancy and childhood, due to a fundamental lack of information, is new and can be important for preventing health risks for vegans. Unsupplemented vegan pregnancies are associated with a higher risk of adverse outcomes [45]. These findings highlight the importance of guideline-based supplementation for vegans during sensitive life stages. The quality of the information sources used by vegans is most likely dependent on the existing attitude of the information providers. If medical experts have a negative attitude towards a vegan diet and DS, their advice may be inadequate—either due to a lack of knowledge about a purely plant-based diet, or because a vegan diet is discouraged per se without providing additional information. Knowledge gaps regarding vegan diets remain common among medical experts, likely due to limited nutrition education and a lack of familiarity with plant-based dietary patterns [44,60]. As a result of limited professional support, many vegan pregnant women turn to alternative sources of information such as books, online platforms, or peer communities to address their specific dietary needs [61]. It is important to know exactly where the information received comes from in order to be able to draw conclusions about its safety and reliability. In a cross-sectional online survey by Fuschlberger et al. [62] among Austrian vegans, 92% reported taking vitamin B_12_ through DS or fortified foods, yet fewer than 10% had consulted a medical expert. However, more research is needed to find out exactly which specific sources of information are being used.

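### Missing DS intake alone cannot support the planned conclusions on deficiency risk and its cause, because the described measures name no food or fortified-food source

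*Protocol article*

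**What the plan says.** **Intended conclusions.** The first secondary objective in section 2.1.2 says that the survey should make recognizable "Risks of nutrient deficiency due to missing intake or incorrect selection of DS because of a lack of food and nutritional health literacy". The compliance objective in the same section moves from dosage form to regularity of administration and on to the development of deficiencies. Statements about how regularly and how long DS are taken "are intended to allow conclusions about the supply of consumers with the corresponding DS and to show any potential dangers or health-enhancing effects". A primary objective in section 2.1.1 says the results "should allow conclusions about the influence of information supply by medical experts on nutrient supply" of pregnant women and children. The Discussion adds that risks to nutrient supply are to be determined, and describes the study as identifying a basic lack of information as the cause of deficiencies.

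**Sources of nutrients.** The Introduction states: "Nutrient deficiency can be prevented by supplying these critical nutrients of a vegan diet adequately, with specific foods or with DS". It also says that a plant-based diet can provide everything needed, "except for a possible lack of docosahexaenoic acid (DHA) and eicosapentaenoic acid (EPA), as well as vitamin B12". The Discussion cites a survey of Austrian vegans in which "92% reported taking vitamin B_12_ through DS or fortified foods, yet fewer than 10% had consulted a medical expert".

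**Measures.** Section 2.5 lists ten questionnaire categories. The one that mentions deficiency is worded around DS. Section 2.7 names users against non-users (for oneself or one's children) as a possible comparison and DS use as an example of a yes/no outcome for logistic regression. Sections 3.1 and 3.2 list DS decisions, compliance, dosage estimates and views on nutritional needs. None of these places names intake from food, fortified foods or nutrient status.

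**The concern.** Whether a person takes DS is a behaviour. Whether a nutrient is adequately supplied is a state that depends on every source. The objectives draw a conclusion about the second from data described only for the first, and the article's own Introduction says the two can differ. A respondent who deliberately uses fortified foods for B12 and one with no B12 source at all give the same answer to a DS yes/no question. The same can hold for infants: the Introduction links a breastfed infant's supply to the mother's, so a child given no DS is not necessarily without a source.

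The cause is also set in advance. Section 2.1.2 attributes the risk to low literacy, and its objective on how vegans conceive of DS treats rejection of DS over health concerns as a possible sign of insufficient education. No described variable separates non-use from ignorance from non-use by informed choice of another source.

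The results are meant to direct advice and prevention. If the two kinds of non-user are mixed, the profile of who needs advice is blurred, and the text on deficiency risk goes further than the data.

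**Working it through.** **Step 1: is there a figure in the plan to reproduce?** No. The article gives no at-risk share, no rule that classifies a respondent as at risk and no expected proportion of DS users. The only figure that bears on the point is the cited 92% for B12 from DS or fortified foods, which leaves 100% − 92% = 8% reporting neither. The documents do not split the 92% into DS and fortified food only.

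**Step 2: what follows from an unsplit 92%?** Let *d* be the share using DS (assumed; not in the documents).

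- DS non-users = 1 − *d*
- Non-users with a fortified-food B12 source = 0.92 − *d*
- Share of non-users with such a source = (0.92 − *d*) / (1 − *d*)

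Per 1000 respondents (the target in section 2.6.1, used here only as a denominator):

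| Assumed DS use *d* | DS non-users | of these, fortified-food source | share | neither |
|---|---|---|---|---|
| 0.92 | 80 | 0 | 0% | 80 |
| 0.90 | 100 | 20 | 20% | 80 |
| 0.85 | 150 | 70 | 47% | 80 |
| 0.80 | 200 | 120 | 60% | 80 |
| 0.70 | 300 | 220 | 73% | 80 |
| 0.50 | 500 | 420 | 84% | 80 |

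The group with neither source stays at 80 throughout, while the DS non-users range from 80 to 500. On the documents alone, the share of non-users who have another B12 source can be anything from none to most.

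**Step 3: the other nutrients.** The Introduction names vitamin B12, zinc, iron, calcium, vitamin D, iodide and omega-3 fatty acids as critical, but limits the possible shortfall of a plant-based diet to DHA, EPA and B12. For a nutrient such as iron, zinc or calcium, the article's own premise does not make DS non-use a deficiency risk by itself. No figure is available for these nutrients.

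**Step 4: can the described variables separate the groups?** The ten categories in section 2.5, the comparisons and models in section 2.7 and the outcomes in sections 3.1 and 3.2 name no variable that would. The limitations in section 5.2 cover self-report, self-selection and the over-representation of women, but not this. The items are in supplementary material that was not available, so a food-source question may exist. Even then, the comparison and the example outcome named in section 2.7 are defined by DS use alone.

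**The case against.** The strongest reply is that the plan contains no such classification. Section 2.7 treats DS use as a behaviour whose influences are modelled, the users/non-users split is only a possible comparison, and section 3.1 bases findings on the frequency of responses. The literacy clause in section 2.1.2 can be read as limiting the objective to non-use that stems from low literacy, which would leave out the informed fortified-food user. This stands in part. A reader might infer that the plan labels every non-user as at risk and will publish an inflated at-risk share. The documents do not support that, since no rule or share is defined. But the stated conclusions about risk and supply remain, and no described variable isolates literacy-driven non-use.

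Second, the article also favours supplementation. It says that "the current state of studies suggests dietary supplementation is necessary", associates unsupplemented vegan pregnancies with adverse outcomes, and cites a review that makes careful supplementation a condition. Naming missing DS intake as a possible risk is therefore not a plain self-contradiction. That stands. However, the same sentence in the Introduction says there are no data on whether the wider range of vegan foods improves supply. Food supply is thus an acknowledged open question that the described measures do not address.

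Third, the 92% is background, concerns B12 only, and comes from Austrian vegans in general rather than pregnant women or children. That stands too, so no particular overstatement factor can be claimed.

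Fourth, a reader might infer that the error always exaggerates risk. It need not. A DS user who takes one product, or the wrong one, may lack other nutrients, and section 2.1.2 itself names incorrect selection.

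**Conclusion.** The point holds in a limited form. The article intends conclusions about deficiency risk and nutrient supply, and about low literacy or lack of information as the cause, from missing or irregular DS intake. With the measures it describes, DS non-use cannot be separated from inadequate supply, so some non-users with another source could be counted as at risk.

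The size is unknown. For B12 the affected share of non-users is 0%, 47% or 60% at DS use of 92%, 85% or 80%. This assumes that the 92% carries over to this sample and that the DS shares are as stated. Having a source does not prove adequate supply, so these shares show who is misdescribed as having no source, not who is well supplied. The verdict concerns what the article says it will conclude. It does not assert that the unseen questionnaire lacks food items.

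**What to change.** Keep DS use yes/no as the behavioural outcome in section 2.7; nothing there needs to change for describing or modelling behaviour.

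Wherever non-use is interpreted as deficiency risk:

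- **If food sources were asked:** report three categories per nutrient, at least for B12: DS; no DS but fortified or specific food; neither. Discuss possible risk from missing intake only for the last. For infants, count formula or the milk of a supplementing mother as a source. This is a rule for classifying answers, not a statement about adequate intake.
- **If food sources were not asked:** limit the conclusion to the statement that the respondent does not use DS. Remove the inference to deficiency risk, and to low literacy as its cause, from section 2.1.2 and the Discussion. Add the missing food-source information to the limitations in section 5.2.

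The cost is a recode in the first case and a change of wording in the second. Neither needs new data, which matters because section 2.8 has the survey closing at the end of July 2025. The downside is a narrower and less striking statement about risk.

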##### Investigation of Conceptualization of Dietary Supplements, with a Special Focus on Their Contribution to Health Maintenance and Optimization from Vegans’ Perspective

The perception of what a DS can achieve, whether it is comparable to medicine or food, or whether a positive/negative effect can be expected, depends on the level of knowledge of vegans about DS. How vegans perceive DS and how they rate their effectiveness influences their intake behavior. What health means for vegans and whether DS are perceived as health-promoting from a vegan perspective should also be clarified.

Determining what is meant by health optimization for vegans creates an understanding of the intake or rejection of DS. Rejection of DS due to health concerns can indicate insufficient education about health benefits.

